## Discussion

In this study, the effect of an evidence based telephone coaching programme (Hartcoach) in addition to usual care is evaluated on the reduction of individual risk factors of patients with CVD. Current programmes do not accomplish that patients with CVD change their lifestyle in a way that their individual risk factors for recurrent coronary events decrease. Hospital based rehabilitation programmes in the Netherlands differ strongly per hospital, both in content and extent. Furthermore, participation rates are rather low. The Hartcoach-programme is a pragmatic intervention that primes the patient to self management by adhering to medication and make relevant behaviour changes. Today’s policy is to enhance self management of patients as a means of improving long-term conditions and secondary prevention.

Patients who are not given the opportunity to follow a rehabilitation programme in the hospital or patients who are not able or motivated to adhere to a hospital based rehabilitation programme, may be reached by a home based programme. Another potential benefit of the Hartcoach-programme may be the positive influence the programme can have on medication adherence. In the Netherlands, statins are prescribed to almost every patient after an acute coronary event, but medication adherence to statins is known to be low. One-year persistence with statins has been estimated to be about 60% in patients with previous cardiovascular events [27-29].

A limitation of the study is the reliance on self report according to two of the primary outcomes, physical activity and diet. Since patients are not blinded to group allocation, this might have an impact on the results. However, both measurements, especially diet, are difficult and laborious to administer in a more reliable and valid manner. Another methodological weakness of the study is the fact that all patients receive usual care next to the Hartcoach-programme and some of the participant may follow a rather intensive rehabilitation programme. Additional effects of the Hartcoach-programme next to intensive rehabilitation may be too small to detect. However, in the Netherlands the Hartcoach-programme is implemented as an additional programme and was never intended to substitute usual care. Thereby, the amount of usual care and contingent cardiac rehabilitation is registered and can be taken into the analyses, while it is expected that there will also be a large number of patients who receive minimal care and support in managing their individual risk factors besides the Hartcoach-programme.

A large Dutch health insurance company (Achmea) already has introduced this programme to a limited number of hospitals and the Hartcoach-programme is offered to their clients. If positive results are found for the Hartcoach-programme, the implementation of the programme will be extended which will have implications for the management of many people with CVD. The Hartcoach-programme can be provided additional to existing services or as a "maintenance" programme for people after cardiac rehabilitation.

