**Discussion:**

This study evaluates the effects of the Hartcoach-programme on the reduction of individual risk factors of patients with CVDs. Patients who are not invited to follow a hospital based rehabilitation programme or patients who are unable to adhere to such a programme, may be reached by this home based Hartcoach-programme. If positive results are found, the implementation of the Hartcoach-programme will be extended, having implications for the management of many people with CVD.

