## Design

A multicenter, randomised parallel-group study will be conducted. The experimental group (Hartcoach-programme plus usual care) will be compared with a control group (usual care only). Four-hundred patients diagnosed with CVD in five hospitals will be included, 200 in each group. Patients are recruited through the participating hospitals and are (in each hospital) randomly assigned to one of the two groups via a computerized procedure at the coordinating research centre (NIVEL). The Hartcoach study had been approved by the Medical Ethics Board of the University of Amsterdam, The Netherlands.

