**Secondary outcomes**		
Blood glucose	fasting glucose < 7 mmol/l	Laboratory
HbA1c (%)	< 53 mmol/mol (< 7%)	Laboratory
Smoking	fully quit	Patient questionnaire: Self report, one question
Self management		Patient questionnaire: Self report, five questions
Medication adherence	Full adherence	Patient questionnaire: Adapted Morisky Scale [22]
Quality of life		Patient questionnaire: MacNew Heart Disease Health-related Quality of Life Questionnaire [23]
Depression Anxiety		Patient questionnaire: Hospital Anxiety and Depression Scale (HADS; [24])

^*^ blood values are analysed by the laboratory in the medical centre the patient is treated, according to local standard practice.

In addition to the outcome measures, also gender, educational status, civil status, work status, the occurrence of life events in the past 12 months, ethnicity, cardiovascular history, treatment history, medication use and co morbidity are registered by the research assistant or nurse at baseline. Data are filled in using an electronic questionnaire.

Through a self developed (paper) patient questionnaire smoking, alcohol consumption, self care strategies in relation to coronary diseases and illness perception are measured. At six months, all measurements are repeated, except measurements of demographic characteristics. In addition, usual care received during the six months is registered through a patient dairy, and patients are asked about their experiences with the Hartcoach-programme.

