### Sample size calculation

Sample size calculation was based on one of the primary outcomes that were also used in the study of Vale et al (2003), namely total cholesterol. Based on the values found by Vale et al (2003) for total cholesterol (between groups difference of 0.36 mmol / L (95% confidence interval: 0.20-0.53 mmol / L) 160 patients per group would be needed to find statistical significant results (power of 0.80 and alpha of 0.05)[17]. In this study, a sample of 200 patients per group is chosen, to account for dropout.

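### Adjusting for usual care recorded in a diary after randomisation can bias the estimate; record rehabilitation status before allocation and keep the diary for description

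*Protocol article*

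**What the plan says.** All references are to the protocol article.

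- **Aim and population.** Objectives of this research asks for the effect of the programme on top of usual care in patients with a coronary event. The Discussion part of the Abstract adds a group that might be reached: "Patients who are not invited to follow a hospital based rehabilitation programme or patients who are unable to adhere to such a programme".
- **Rehabilitation in both arms.** Intervention lets usual care include cardiac rehabilitation, in either group. Patients whose rehabilitation is chiefly aimed at lifestyle are excluded, and Participants has a matching exclusion.
- **The admitted weakness.** The Discussion notes that some participants may follow a fairly intensive rehabilitation programme and continues: "Additional effects of the Hartcoach-programme next to intensive rehabilitation may be too small to detect". It answers that the amount of usual care and rehabilitation is registered and can be used in the analysis.
- **The record.** Under Outcomes, in the text after Table 1: "usual care received during the six months is registered through a patient dairy". The baseline list there includes cardiovascular and treatment history but names no rehabilitation referral, offer or uptake.
- **The analysis rule.** Intervention states that if the amount or type of usual care differs between the groups, the analysis will adjust for it. The covariates listed under Statistical analysis are patient characteristics and do not include care received.

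**The concern.** The protocol names a problem and offers a remedy, and the remedy is the weak part. Care received after allocation is an outcome of the allocation as much as a background condition. Step 3 of the coaching cycle trains patients to be assertive with their doctor, so coached patients may take up more care. They may also take up less, if the coach meets the need. Either way the arms would differ in diary-recorded care because of the treatment, and that difference is what switches the adjustment on.

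Two things then go wrong. If the people who attend rehabilitation differ in prognosis, conditioning on attendance makes the arms no longer comparable. If rehabilitation itself affects the risk factors, adjustment also removes whatever part of the programme's effect runs through it. The same applies to an effect reported separately for diary-defined attenders and non-attenders. Such a split is the natural way to look at the patients named in the Abstract, and nothing listed at baseline clearly supports another.

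**Working it through.** **1. What each source of rehabilitation data can support**

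| Source | Timing | Can allocation change it? |
|---|---|---|
| Exclusion of similar lifestyle interventions (Participants) | Entry | No, but it does not classify those who remain |
| Treatment history (Outcomes) | Baseline | No, but its content is not defined |
| Usual-care diary (Intervention, Outcomes) | Six months after randomisation | Yes |

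Only the diary is described as recording rehabilitation, and only the diary feeds the adjustment.

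**2. The plan's own figure**

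Sample size calculation uses a "between groups difference of 0.36 mmol / L (95% confidence interval: 0.20-0.53 mmol / L" and concludes that "160 patients per group would be needed to find statistical significant results (power of 0.80 and alpha of 0.05". No SD is given. Taking a two-sided test, solve n = 2·SD²·(1.96 + 0.8416)²/δ² for the SD:

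SD = 0.36 × √(160 / (2 × 7.849)) = 1.149 mmol/L.

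The quoted interval gives SE = (0.53 − 0.20)/(2 × 1.96) = 0.0842. This yields an SD only if the earlier trial's arm size is assumed: 300 per arm gives 1.03 (n = 129), and 400 per arm gives 1.19 (n = 172). So 160 is plausible but cannot be reproduced from the document. The step to 200 fits a 20% dropout: 160/0.80 = 200. SD 1.149 is used below as an assumption.

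**3. Does the diary adjustment bias the estimate?**

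The simulation had 2,000,000 patients per scenario and 1:1 allocation *t*. An unmeasured prognostic factor *u* ~ N(0,1) drives both attendance and outcome:

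- attendance R = 1 if 0.8*u* + *s·t* + logistic noise > 0.4
- outcome y = −0.36*t* − 0.4*u* + N(0, 1.07²), with no effect of R itself

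Here *s* is the effect of coaching on attendance. All these values are assumptions.

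| *s* | Attendance, coached / control | ITT | Non-attenders only | Adjusted for R |
|---|---|---|---|---|
| 0 | 41% / 41% | −0.357 | −0.358 | −0.357 |
| +0.5 | 52% / 41% | −0.358 | −0.327 | −0.328 |
| −0.5 | 31% / 41% | −0.358 | −0.386 | −0.387 |

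When coaching leaves attendance alone, neither conditional estimate is biased. When it shifts attendance by about 10 percentage points, both move by about 0.03, which is 0.030/0.358 = 8% of the effect. At 160 per arm the standard error of the difference is 1.149 × √(2/160) = 0.128, so the bias is about a quarter of one standard error. The intention-to-treat estimate does not move in any scenario.

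**4. What a baseline-defined subgroup could deliver**

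Assume half of 160 evaluable patients per arm fall in each stratum, so 80 per arm.

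- 95% CI half-width in one stratum: 1.96 × 1.149 × √(2/80) = 0.356 mmol/L.
- SE of the interaction: 1.149 × √(2/80 + 2/80) = 0.257.
- Power to separate 0.36 from 0.18: difference/SE = 0.18/0.257 = 0.70, giving about 11% two-sided.

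This is enough to report an estimate with its uncertainty, not to test for a difference.

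**The case against.** Much of the case on the other side stands. The aim is an add-on effect in all enrolled coronary patients. Rehabilitation is permitted in both arms, so the randomised comparison answers that aim. The form of rehabilitation closest to the coaching is excluded at entry. The dilution is disclosed as a limitation. No rehabilitation subgroup is announced, and an article may leave subgroup definitions and form items to fuller documents. The bias arises only if allocation changes care, and on the assumptions above it is modest.

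A reader might go further and infer that the trial cannot validly estimate the effect in the patients it is meant for. The document does not support that. Patients outside rehabilitation are a group that may be reached, not an eligibility-defined target, and the Discussion describes the programme as additional to usual care. Dilution affects the size of the effect, the power and the reach of the result, not validity.

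A reader might also infer a serious power loss. If the effect is 0.36 without rehabilitation and 0.18 with it, the pooled difference is 0.36(1 − f) + 0.18f. At attendance f of 30%, 50% and 70% this is 0.31, 0.27 and 0.23, with power 66%, 56% and 44% at 160 per arm. The arithmetic is right, but neither the attendance share nor the halving is in the document. The 0.36 is the earlier trial's overall difference and may already average over a similar mix.

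The closing remark about maintenance use after rehabilitation concerns implementation and is not a claim the trial makes.

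None of this rescues the adjustment rule. It is stated in the article, it acts on post-randomisation care, and it is triggered by an observed difference between arms whether chance or coaching produced it.

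**Conclusion.** The point holds as a fault in the stated remedy, not in the trial's main comparison. The intention-to-treat estimate of the add-on effect in the enrolled mix is valid. Adjusting it for diary-recorded care, or splitting it by that care, can bias it when coaching changes uptake, which is a situation that triggers the rule. In the illustration the shift is about 0.03 mmol/L on 0.36, in either direction. Its size depends on the assumed link between prognosis and attendance and on the assumed change in attendance, and it is zero if coaching leaves care unchanged. The article describes no explicit baseline rehabilitation item that would avoid the problem. The change is worth making because it is cheap and because status before allocation is hard to recover later.

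**What to change.** 1. **Outcomes, baseline list.** Add one item to the electronic T0 form: cardiac rehabilitation referred or started; offered but declined or not able; not offered. The article places T0 after consent and before the programme starts, without saying that it precedes allocation, so the portal should require this item before it releases the assignment.
2. **Intervention, usual-care paragraph.** Replace the conditional adjustment with a description of diary-recorded care by arm. If a model adjusted for diary care is still wanted, label it a sensitivity analysis.
3. **Statistical analysis.** State that the primary result is the intention-to-treat estimate, not adjusted for care received after randomisation.
4. **Effect outside rehabilitation.** If one is to be reported, pre-specify it by the baseline item, with 95% CI and the interaction, as estimation only.
5. **Discussion.** Point the sentence about using registered care in the analysis to items 2 to 4.

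The cost is one extra baseline question and a few sentences. Subgroup estimates will be imprecise (about ±0.36 mmol/L at an assumed 80 per arm and SD 1.149), and status at T0 is not the same as later attendance. The Abstract describes the study as under way. For patients already randomised, the item could be filled only from hospital records dated before allocation, where these exist.

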## Endnotes

^a^ During the study, we will try to find additional funding for a measurement at 12 months. This would not only provide a follow-up measurement but will also change the study design as the control group is invited to follow the Hartcoach-programme after completion of the six months measurement.
